### Objectives and outcome measures

The primary objective is to demonstrate superiority of ultrafiltration and dialysate conductivity regulation (UCR) and/or ultrafiltration and temperature regulation (UTR) over conventional hemodialysis, in preventing intra- and post-dialytic complications, when fluid-overloaded hemodialysis patients receive systematic fluid reduction, to reach a final dry weight of normohydration weight −7% of ECW postdialysis. The primary outcome measure is the total number of hemodialysis sessions per patient that were accompanied, intra- or post-dialytically, by at least one symptom most likely related to fluid withdrawal (as specified in Table1), divided by the number of hemodialysis sessions at risk (as by study protocol: 12 sessions per patient in study phase 1). Both groups, UCR and UTR, will be compared against the conventional hemodialysis group, and afterward against one another, using the two-sided Student’s *t* test

**Table 1 T1:** Complications related to fluid withdrawa

(1)	Intradialytic cramping
(2)	Intradialytic hypotension (>40 mmHg SBP) within 30 minutes: clinically asymptomatic
(3)	Intradialytic hypotension (>40 mmHg SBP) within 30 minutes: clinically symptomatic
(4)	Clinically symptomatic intradialytic hypotension: unspecified drop in SBP
(5)	Unspecified intradialytic complication, most likely related to fluid withdrawal
(6)	Patient-reported postdialysis complication, most likely related to fluid withdrawal

The secondary objectives are:

(a). To demonstrate superiority of ultrafiltration and dialysate conductivity regulation (UCR) and/or ultrafiltration and temperature regulation (UTR) over conventional hemodialysis, in preventing specific intradialytic complications:when fluid-overloaded hemodialysis patients receive systematic fluid reduction, to reach a final dry weight of normohydration weight −7% of ECW postdialysis. The secondary outcome measure for objective (a) is the total number of hemodialysis sessions per patient which were accompanied by the respective symptom most likely related to fluid withdrawal (1 to 6), divided by the number of hemodialysis sessions at risk (as by study protocol: 12 sessions per patient in study phase 1). Both groups, UCR and UTR, will be compared against the conventional hemodialysis group, and afterward against one another, using the two-sided Student’s *t* test.

1. intradialytic cramping

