#### Dry weight reduction

The BCM measurement for fluid overload is provided in kilograms and percentage of ECW. A patient’s new dry weight is calculated as follows: (Predialysis body weight – (fluid overload + 7% ECW)). Thus it is the normohydration weight −7% ECW, and serves as the new, BCM- determined, ideal, or ‘final’ dry weight. In order to reach this ‘final’ dry weight, the patient’s previous dry weight is decreased as previously described in the ‘Dry-Weight Reduction in Hypertensive Hemodialysis Patients’ (DRIP) trial [11]: by 0.1 kg per 10 kg body weight at every hemodialysis session until the final dry weight is reached or any intradialytic complications (listed in Table1) may occur.

An exemplary dry weight reduction scenario is provided in Figure 2. In the event of the first intradialytic complication, standardized clinical interventions take place as listed in Table2, and the dry weight of the ongoing hemodialysis session is re-adjusted to the dry weight of the previous hemodialysis session. At the subsequent hemodialysis session, the dry weight is prescribed as 50% of the previous, additional fluid removal, and all further dry weight reductions are prescribed accordingly. In the event of the second intradialytic complication, standardized clinical interventions take place, and the dry weight at the ongoing hemodialysis session is re-adjusted to the dry weight of the previous hemodialysis session, as before. At the subsequent hemodialysis session, fluid removal is further reduced by 50% of the corrected, additional fluid removal, or to a minimum of 200 g (whatever occurs first, depending on the overall weight of the patient). In the event of a third intradialytic complication, standardized clinical interventions take place, and the dry weight at the ongoing hemodialysis session is re-adjusted to the dry weight of the previous hemodialysis session, as before. No further attempts are made to reduce the dry weight during this study period, unless the patient did not yet reach reduction steps of 200 g.

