### Statistical analysis plan

The statistical analysis plan (SAP) provides full details regarding the analyses, the data display, and the algorithms to be used for data derivations. The SAP includes the definition of major and minor protocol deviations, which will be identified by medically trained staff before the study closure. Safety and tolerability are analyzed descriptively. Safety analysis is performed on the intention-to-treat (ITT) population. All secondary endpoint analyses are exploratory in nature.

Sample size calculation: for the primary endpoint analysis, we will assess the differences in intradialytic complications between the three study groups, only during the first study phase. Based on a typical occurrence of 0.14 dialysis-related complications per patient-day at risk in the conventional hemodialysis group [20], two-sided testing and an expected standard deviation of 10%, an alpha = 0.05 and a beta = 0.2, a sample size of 17 patients per group was determined to detect a minimum difference of 10% between groups. The UCR and UTR groups will be tested against the conventional hemodialysis control group, and afterward against one another. We expect a drop-out rate of approximately 10%. Individuals who do not complete the study cannot be replaced, because we do not include patients with hemodialysis vintage <3 months, and all patients who qualify for the study are asked to participate after the initial BCM measurement at all three centers. Thus, the study sample was determined to consist of 60 patients with ECW ≥15%, by BCM measurement. If patients are lost to follow-up, they will be excluded from the analysis

Two different analysis sets are defined for safety and efficacy, respectively. The efficacy of UCR and UTR will be assessed in all subjects who received the study method (at least once) and did not violate the protocol in a way that might affect the evaluation of the effect of the study method on the primary objective, that is, without major protocol violations. The per-protocol set is employed in the analysis of efficacy variables. The safety analysis set includes subjects who were randomized and received at least one study method (modified intention-to-treat). The safety set is employed in the analysis of tolerability and safety variables. Statistical analysis is performed with SAS.

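### The primary t tests leave out the prescribed dry-weight reduction known from the enrolment BCM; adjusting for it in one three-arm model would be a small, nearly free gain in efficiency

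*Protocol article*

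**What the plan says.** The section on objectives and outcome measures defines one proportion per patient: sessions with at least one listed complication, divided by sessions at risk ("as by study protocol: 12 sessions per patient in study phase 1"). It then fixes the comparisons, each by a two-sided Student's t test: "Both groups, UCR and UTR, will be compared against the conventional hemodialysis group, and afterward against one another". No covariate is named.

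The sample size paragraph, under the statistical analysis plan heading, rests on the same unadjusted comparison. It starts from a control rate ("Based on a typical occurrence of 0.14 dialysis-related complications per patient-day at risk in the conventional hemodialysis group") and takes "an expected standard deviation of 10%, an alpha = 0.05 and a beta = 0.2, a sample size of 17 patients per group was determined".

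Three other statements bear on the point:
- **Study setting and organizational details.** Overload of at least 15% of extracellular water by BCM is an inclusion criterion, so every randomised patient has an enrolment BCM value. Randomisation is stratified by centre only.
- **Dry weight reduction.** The target follows from the BCM result ("new dry weight is calculated as follows"). It is approached in steps of 0.1 kg per 10 kg body weight until it is reached or complications intervene.
- **Study setting, again.** BCM is repeated before every run-in and shortly before time zero. The run-in lasts up to twelve sessions for UCR and up to six for UTR; conventional haemodialysis has none.

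**The concern.** Patients enter phase 1 with different amounts of weight to lose. Someone far from target faces more reduction steps within the same twelve sessions than someone close to it, and complications are expected to arise from those steps. The amount prescribed at enrolment is known before allocation, yet neither the stratification nor the test uses it. Whatever outcome variance it predicts stays in the error term.

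Two things are at stake in arms of 17 to 20. The first is some power. The second is that a chance imbalance in prescribed reduction moves the unadjusted estimate. The article says that patients who drop out cannot be replaced and that all qualifying patients are already approached, so the analysis is the easiest place left to gain precision.

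**Working it through.** **Inputs from the article.** Difference 10 points, SD 10%, two-sided alpha 0.05, power 80%, 17 per group (statistical analysis plan section); control rate 0.14; 12 sessions per patient.

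**Assumed inputs.** R2 is the share of within-arm outcome variance explained by the prescribed reduction. The documents do not give it; I use 0 to 0.10. Simulating the step-down rule with assumed weights, overload and session risks puts prescribed steps alone at 1 to 10%. SD 13% is an assumed alternative.

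**Step 1: the plan's own figure.** Noncentrality = 0.10 / (0.10 × sqrt(2/17)) = 2.915, with 32 degrees of freedom and critical value 2.037. Power is 80.7%; 16 per group gives 78.1%. The stated 17 is correct. At 20 per group the t test has 86.9%.

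**Step 2: one model over three arms, one covariate.** With N = 3 × 17 = 51, the residual degrees of freedom are 51 − 3 − 1 = 47 (critical value 2.012). Estimating one covariate slope multiplies the variance of an arm difference by 1 + 1/(N − 5) = 1 + 1/46 on average. So

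noncentrality = 0.10 / (SD × sqrt((2/17) × (1 − R2) × (1 + 1/46))).

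| SD | t test | R2 = 0 | R2 = 0.05 | R2 = 0.10 |
|---|---|---|---|---|
| 10%: noncentrality | 2.915 | 2.884 | 2.959 | 3.040 |
| 10%: power | 80.7% | 80.6% | 82.6% | 84.6% |
| 13%: noncentrality | 2.243 | 2.219 | 2.276 | 2.339 |
| 13%: power | 58.5% | 58.4% | 60.6% | 63.0% |

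The near-zero loss at R2 = 0 arises because pooling the error over three arms offsets the covariate's cost. A three-arm model without any covariate would have 81.5% at SD 10% (48 degrees of freedom), so a worthless covariate costs 0.9 point against that model and 0.1 point against the planned t test.

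**Step 3: chance imbalance.** The standard error of a between-arm difference in a covariate is sqrt(2/17) = 0.34 covariate SDs. At R2 = 0.10, an imbalance of that size shifts the unadjusted estimate by 0.34 × sqrt(0.10) × SD: about 1.1 points at SD 10% and 1.4 points at SD 13%, against a target of 10.

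**Step 4: how much can any covariate explain?** Binomial noise alone at 14% over 12 sessions gives sqrt(0.14 × 0.86 / 12) = 0.100. The planned SD of 10% is therefore already the floor in the control arm and leaves no between-patient variance there. At a rate of 4% the floor is sqrt(0.04 × 0.96 / 12) = 0.057. If the SD were still 10% in that arm, up to (0.0100 − 0.0032) / (11/12) / 0.0100 = 0.74 of its variance would be between patients. The ceiling averaged over the two arms is about 0.37. At SD 13% and 14%, the control-arm between-patient share is (0.0169 − 0.01003) / (11/12) / 0.0169 = 0.44. The SD 13% row is thus the more coherent setting for a gain.

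**The case against.** The strongest reply is that nothing here is wrong. Randomisation makes the unadjusted test valid, the sample size reproduces, and the plan meets its 80% target on its own inputs. Supportive adjusted models may also sit in the separate analysis plan, which is not shown. All of that stands, and it limits the point to efficiency. It does not remove the point, because the article itself states the primary test.

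A second reply is that the enrolment BCM does not finally settle how many steps a patient takes, because the measurement is repeated before run-in and before time zero. That also stands. The enrolment value is a proxy for the operative prescription, which weakens it as a predictor. It remains the version to use, because the later values follow randomisation and a run-in whose length differs by arm.

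A reader might go further and infer that the plan wastes substantial power, and that adding each patient's pre-study complication rate would lift it to around 90%. The documents do not support this:
- They describe no collection of pre-study complications. Complications go on the study case report form, some in categories worded for this study, so the rate would need retrospective chart abstraction under a different definition. Antihypertensive withdrawal and the switch from haemodiafiltration would also separate those sessions from the study sessions.
- Power figures of 89% to 93% at SD 10% need an R2 of 0.20 to 0.33. In the control arm, that SD leaves no patient heterogeneity to explain (step 4).
- Even at SD 13%, a twelve-session history with perfectly stable risk could explain at most about 0.44² ≈ 0.20 in that arm.

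**Conclusion.** The point holds as a modest, low-cost improvement. The plan fixes three unadjusted t tests while a plausible predictor, available for every patient before randomisation, goes unused. Against the planned t test at 17 per group, adjustment changes power by −0.1 to +3.9 points at SD 10% and by −0.1 to +4.5 points at SD 13%.

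This rests on an assumed R2 of 0 to 0.10, a linear covariate effect, and a common residual SD across arms. Student's t test already makes the last assumption for each pair; the three-arm model extends it to all three. The case for acting is that almost nothing is lost if the covariate proves useless. It is not that a large gain has been shown.

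**What to change.** Make the primary analysis one linear model on the per-patient proportion over all three arms. Its terms are arm and the dry-weight reduction prescribed from the enrolment BCM, expressed in steps of 0.1 kg per 10 kg body weight. Report the three adjusted pairwise differences with 95% confidence intervals, and keep the t tests as supportive.

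State that the covariate is the pre-randomisation value. Do not use BCM values repeated after randomisation or anything from the run-in, and do not add a chart-abstracted complication history.

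The cost is a wording change and one degree of freedom. The enrolment BCM is already measured, so no new data collection or extra patients are needed. Because treatment is open and recruitment has begun, date the change before any comparison of outcomes by arm.

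Suggested wording: *The proportion of phase 1 sessions with a complication will be analysed by a linear model with study arm as a factor and the dry-weight reduction prescribed at the enrolment BCM measurement as a continuous covariate. Adjusted pairwise differences will be given with 95% confidence intervals; unadjusted t tests will be supportive.*

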2. clinically asymptomatic, intradialytic hypotension (>40 mmHg drop in systolic blood pressure (SBP) within 30 minutes)

3. clinically symptomatic, intradialytic hypotension (>40 mmHg drop in SBP within 30 minutes)

4. clinically symptomatic, intradialytic hypotension (even if it is not possible to identify a sudden drop in blood pressure, for example, patients may slowly move towards low blood pressure values (f. ex. below 100 mmHg SBP), and report symptoms)

5. unspecified intradialytic symptoms or events, which are most likely related to fluid withdrawal

6. patient-reported postdialysis complication, most likely related to fluid withdrawal (All of the above also listed in Table1)

(b). To demonstrate superiority of UCR and/or UTR over conventional hemodialysis in allowing patients to reach a lower body weight, relative to his/her postdialysis weight at the beginning of study phase 1 (time zero). The secondary outcome measure for objective (b) is the difference in postdialysis body weight from time zero to the end of study phase 1, divided by the postdialysis body weight at time zero.Example: if a patient has a postdialysis body weight of 65 kg at time zero (the last hemodialysis session before the first dry weight reduction), and reaches a postdialysis body weight of 62 kg at the end of the first study phase, his difference in body weight will be 65 kg – 62 kg = 3 kg. Relative to this patient’s postdialysis body weight at time zero, weight reduction from beginning to end of study phase 1 will be 3/65*100 = 4.61%.The relative weight reduction in both groups, UCR and UTR, will be compared against the conventional hemodialysis group, and afterward against one another, using the two-sided Student’s *t* test.

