**Figure 2 F2:**
[figure not shown]
An exemplary dry weight reduction scenario.

**Table 2 T2:** Clinical interventions

	**1**^**st**^**intervention**	**2**^**nd**^**intervention**	**3**^**rd**^**intervention**	**4**^**th**^**intervention**
Cramping	20 mL NaCl (1 M)*	according to doctor's order		
Nausea	Trendelenburg position	250 mL NaCl (0.9%)	plasma expander	according to doctor's order
Vomiting				
Clinically symptomatic IDH				
Decrease in intradialytic SBP ≥40 mmHg				
Unspecified	according to doctor's order			

*5.85% weight/volume. *IDH* intradialytic hypotension, *M* molar, *NaC1* sodium chloride, *SBP* systolic blood pressure.

At the occurrence of symptoms, ultrafiltration is decreased and dry weight adapted, as per the study’s protocol.

Justification for the duration of the study phase: 12 hemodialysis sessions per study phase imply that, if regulated ultrafiltration can prevent intra- and post-dialytic complications, a 70 kg patient is, in theory, able to remove as much as 12 × 700 g = 8.2 L of excess fluid within one study phase. Therefore, we expect that for the great majority of patients, we would theoretically be capable of removing all excess fluid within one study phase.

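### Secondary outcome (b), relative weight reduction, is to be compared by an unadjusted t test, although each patient's loss is limited by a prescribed reduction already known at time zero

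*Protocol article*

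**What the plan says.** In the protocol article, Objectives and outcome measures, objective (b) is to show that regulation of ultrafiltration with conductivity (UCR) or with temperature (UTR) is superior "in allowing patients to reach a lower body weight, relative to his/her postdialysis weight at the beginning of study phase 1 (time zero"). The outcome is the "difference in postdialysis body weight from time zero to the end of study phase 1, divided by the postdialysis body weight" at time zero. A worked example takes a patient from 65 kg to 62 kg: "weight reduction from beginning to end of study phase 1 will be 3/65*100 = 4.61" percent. On analysis: "The relative weight reduction in both groups, UCR and UTR, will be compared against the conventional hemodialysis group", and then the two regulated arms against each other, each time by a two-sided Student's t test. No covariate is named.

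The section Dry weight reduction sets the target for each patient as predialysis weight minus the sum of fluid overload and 7% of extracellular water (ECW): "Thus it is the normohydration weight −7% ECW, and serves as the new, BCM- determined, ideal, or ‘final’ dry weight". The previous dry weight is lowered "by 0.1 kg per 10 kg body weight at every hemodialysis session until the final dry weight is reached" or a complication occurs. In the justification for the length of a study phase, the authors write that "we expect that for the great majority of patients, we would theoretically be capable of removing all excess fluid within one study phase".

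Entry requires overload of at least 15% of ECW, with no upper limit. Randomization is stratified by center only. The Statistical analysis plan section calls all secondary endpoint analyses exploratory.

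**The concern.** Two rules meet here. Weight loss is divided by body weight, but how much loss a patient can show is limited by a target that differs between patients. For a patient who reaches target, outcome (b) equals the prescribed reduction over body weight, whichever machine was used. For a patient who stops short, it reflects how many steps were tolerated. Variation in the prescribed reduction therefore enters the outcome without saying anything about the technique.

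The prescribed reduction is fixed before the first reduced session, so the analysis could remove this variation. An unadjusted t test does not. With 60 patients in three arms, a real difference in tolerated fluid removal is easier to miss, and a chance difference between arms in starting excess passes straight into the estimate.

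**Working it through.** **1. The protocol's own figure.** 3/65 × 100 = 4.615%. The protocol prints 4.61, so the example reproduces (truncated).

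**2. How the prescribed reduction enters.** Outcome = share of prescription achieved × prescribed reduction / body weight. At 65 kg:

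| Prescribed reduction | Share achieved | Outcome (b) |
|---|---|---|
| 1.5 kg | 100% | 2.31% |
| 3 kg | 100% | 4.62% |
| 6 kg | 100% | 9.23% |
| 6 kg | 50% | 4.62% |

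Full achievement scores anywhere from 2.31% to 9.23%, and half of 6 kg ties with all of 3 kg.

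**3. Plausible spread of the prescribed reduction.** The documents give no distribution. Assume 70 kg body weight, ECW 18 L, overload 15 to 25% of ECW, and 1.5 to 2.5 kg gained between sessions. Then gap = (overload fraction + 0.07) × 18 − gain.
- Smallest: 0.22 × 18 − 2.5 = 1.46 kg. Largest: 0.32 × 18 − 1.5 = 4.26 kg.
- At 0.7 kg per session (0.1 kg per 10 kg), that is about 2 to 6 uninterrupted sessions out of 12.
- With uniform inputs the variance is 1.8²/12 + 1²/12 = 0.353, so the SD is about 0.6 kg.
- The largest SD possible on this range, with half the patients at each end, is (4.26 − 1.46)/2 = 1.4 kg.

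**4. Chance imbalance.** Arms are 60/3 = 20. The standard error of the difference in mean gap is SD × √(2/20): 0.6 × 0.316 = 0.19 kg, or 1.4 × 0.316 = 0.44 kg.

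**5. Power with and without adjustment.** Simulations used 20 per arm and mean gap 2.7 kg. Model A makes loss a share of the gap: mean 75% v 90%, SD 20 points, capped at 100%. Model B makes tolerated loss independent of the gap: 1.5 v 2.1 kg, SD 0.7 kg, capped at target. All of these values are assumptions.

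| Gap SD | A: t test | A: adjusted | B: t test | B: adjusted | B: percent of prescription |
|---|---|---|---|---|---|
| 0.6 kg | 26% | 58% | 71% | 71% | 62% |
| 1.0 kg | 17% | 54% | 58% | 63% | 49% |
| 1.4 kg | 13% | 49% | 48% | 56% | 38% |

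A separate set of runs of both models gave 13–27% rising to 50–58% under A, and 43–62% rising to 53–65% under B. In those runs the variance of the arm difference fell by a factor of about 1.05 to 5.5 overall, and by about 1.1 to 2.5 at a gap SD of 0.6 kg.

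A third set used 18 per arm, a mean prescription of 4% of body weight with coefficient of variation 0.2 to 0.5, achieved share averaging 0.50 or 0.65 (SD 0.15 or 0.25), and a true difference of 0.20 in that share. Power was 24–83% unadjusted and 54–96% adjusted.

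**6. False positives.** With no true effect, the unadjusted test in the third set rejected in 4.5 to 5.9% of runs. The adjusted test also stayed near 5%.

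**The case against.** The strongest reply is that the outcome does what the objective asks. Objective (b) speaks of a lower body weight relative to the patient's own starting weight, not of reaching target. Steps are themselves proportional to body weight, so body weight is a natural denominator for patients who stop short. This stands, and it is why the outcome should be kept.

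A reader might go further and infer that outcome (b) mostly measures starting fluid excess. The documents do not support that. They give no distribution of prescribed reduction or of achievement. Across assumed values, the squared correlation of the outcome with the prescribed reduction ran from 0.09 to 0.81. The expectation that most patients could remove all excess is explicitly theoretical, and complications halve the step and can end further reduction.

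A reader might also want to replace the outcome by the percentage of the prescription achieved. That changes the question being answered and loses power in every row under model B. It is also unstable when the prescribed reduction is small.

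Model A favors adjustment by construction, since loss is generated as a share of the gap. That is fair, and is why model B is shown beside it: there the gain is 0 to 8 points.

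Finally, the endpoint is exploratory, no power is claimed for it, and a fuller analysis plan exists that is not shown. The exploratory status limits the weight of the point. The unseen plan might add a covariate, but the article itself fixes the outcome and the test.

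**Conclusion.** The point holds as one about precision. Outcome (b) is limited by a patient-specific prescription, and the planned test ignores that known quantity. Randomization balances the prescription in expectation and the test keeps its level, so there is no bias from this source. Exclusions from the per-protocol set could weaken that protection, but that is a separate matter.

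The loss could be negligible or substantial. Adjustment reduces the variance of the arm difference by a factor of about 1.05 to 5.5. The upper end needs loss to scale with the gap and the gap SD to be near its maximum on the assumed range. At an SD of about 0.6 kg the factor is about 1.1 to 2.5. These figures rest on the assumed ECW, overload, weight gain and achievement in the working, none of which the documents give. In the simulations adjustment cost no appreciable power, so the change is worth making even though the outcome is secondary and exploratory.

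**What to change.** Leave outcome (b) as defined. Replace the t tests for it with a linear model (ANCOVA) containing treatment arm and the prescribed reduction at time zero, that is, previous dry weight minus BCM-determined final dry weight, as a percentage of body weight. Use the time-zero value even if the target is later re-set after a repeat BCM measurement, which Study setting and organizational details allows. A value from after the start could itself be affected by treatment.

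The percentage of the prescription achieved may be reported descriptively, but should not replace the outcome.

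One definition needs reconciling first. Objective (b) places time zero at the last session before the first reduction, whereas Study setting and organizational details places it at the first session with reduction. The difference can move the outcome by about one step, or 1% of body weight.

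The cost is one sentence in objective (b) and one covariate in the program. Both weights are already needed to set the dry weight prescription, so no new data or patients are required.
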